### Informed Consent

In case an older adult is willing to participate in the study, a researcher (HN) will explain the study and will provide the participant with the study information sheet, information form for the general practitioner, and their permission to participate in the study and consent form. Participants will be informed that in this study there are two types of interventions that expose the participants to perturbations during treadmill walking (random PBBT vs. block PBBT); both are expected to improve balance function. To maintain the motivation of older adults to participate, they will be offered to participate in “other” exercise programs after the training period. They are also informed that the training might be difficult in the beginning and thus some muscle soreness will occur and that participants are free to withdraw from the study at any time point, without consequence. Participants may also be withdrawn from the study due to changes in their health status that affect eligibility. HN will answer the participant questions about the study. Participants may discuss the study with their family members, friends, or healthcare providers. The informed consent process will be documented by research personnel.

### Interventions

Block PBBT will be trained using a foretold magnitude and unidirectional perturbations during treadmill walking. The random PBBT will be trained using a computer-generated random multidirectional unexpected perturbation during treadmill walking. Each group will receive eight training sessions, twice a week for 4 weeks (Figure 2, Table 3, details of the training programs). Each session will last 20–30 min and will include 2 min of warm-up walking at participants’ preferred speed without any perturbations and 14–20 min of 35 unexpected perturbations while walking (based on the group motor learning technique). In the random PBBT, the perturbations will be given randomly every 20–40 s, and the training will end with a 2-min cool-down comfortable walking. The participants in the block PBBT group will be aware of the direction of the perturbation, given visual cues, and in each training session, only one perturbation direction will be trained. The goal of both training protocols (random PBBT and block PBBT) is mainly directed towards a cognitive understanding of the training and an improvement of self-confidence for exercises on higher perturbation magnitudes. Some general effects on muscle power and speed development, coordination, and conditioning (i.e., endurance) are expected. Everyone should progress to a higher perturbation magnitude (Figure 2, Table 3, the training programs).

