## Abstract

**Introduction**: Falls are the leading cause of fatal and nonfatal injuries among older adults. Studies showed that older adults can reduce the risk of falls after participation in an unexpected perturbation-based balance training (PBBT), a relatively novel approach that challenged reactive balance control. This study aims to investigate the effect of the practice schedule (i.e., contextual interference) on reactive balance function and its transfer to proactive balance function (i.e., voluntary step execution test and Berg balance test). Our primary hypothesis is that improvements in reactive balance control following block PBBT will be not inferior to the improvements following random PBBT.

**Methods and Analysis**: This is a double-blind randomized controlled trial. Fifty community-dwelling older adults (over 70 years) will be recruited and randomly allocated to a random PBBT group (*n* = 25) or a block PBBT group (*n* = 25). The random PBBT group will receive eight training sessions over 4 weeks that include unexpected machine-induced perturbations of balance during hands-free treadmill walking. The block PBBT group will be trained by the same perturbation treadmill system, but only one direction will be trained in each training session, and the direction of the external perturbations will be announced. Both PBBT groups (random PBBT and block PBBT) will receive a similar perturbation intensity during training (which will be customized to participant’s abilities), the same training period, and the same concurrent cognitive tasks during training. The generalization and transfer of learning effects will be measured by assessing the reactive and proactive balance control during standing and walking before and after 1 month of PBBT, for example, step and multiple steps and fall thresholds, Berg balance test, and fear of falls. The dependent variable will be rank transformed prior to conducting the analysis of covariance (ANCOVA) to allow for nonparametric analysis.

**Discussion**: This research will explore which of the balance retraining paradigms is more effective to improve reactive balance and proactive balance control in older adults (random PBBT vs. block PBBT) over 1 month. The research will address key issues concerning balance retraining: older adults’ neuromotor capacities to optimize training responses and their applicability to real-life challenges.

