The process of skill acquisition relies on the interaction between cognition and motor control. One demonstration of this interaction has been termed the contextual interference (CI) effect (Lee and Magill, 1983). For example, practice schedule, the influence of the order in which training materials are presented to the learner, may influence learning abilities (Jamieson and Rogers, 2000). In training programs, the practice schedule is mainly divided into blocked or random practice. We define blocked practice as practicing a single task repeatedly before moving on to the next task (for example, train only unexpected loss of balance to the right direction, i.e., right balance reactive stepping, in a specific training session). Random practice is defined as practicing the tasks in a pseudo-random order (Shea and Morgan, 1979) such that each task is not practiced consecutively (for example, train balance recovery, including reactive stepping to the right/left/forward/backward randomly at the same training session). There is evidence that suggests that random training can improve motor learning [from pressing a button in response to a light cue, automated teller machine (ATM) operation, hand grasp as a response to a stimulus and knocking down six (changing) barriers, isometric pinch force to perturbation training, et cetera (Shea and Morgan, 1979; Del Rey, 1982; Kausler et al., 1990; Jamieson and Rogers, 2000; Guadagnoli and Lee, 2004; Bhatt and Pai, 2009; Mansfield et al., 2010; Hurt et al., 2011; Bhatt et al., 2012; Fazeli et al., 2017)]; on the other hand, others suggest that block training (cognitive memory task, balance perturbation training, seat to stand training, and isometric pinch force control) is more effective (Del Rey, 1982; Lazarus and Haynes, 1997; Pavol et al., 2002, 2004; Lin et al., 2008; Van Ooteghem et al., 2009; Pai et al., 2014a, b; Dijkstra et al., 2015; Coelho and Teixeira, 2017, 2018; Coelho et al., 2018). Additionally, a high CI effect (i.e., random practice) may create a poorer performance acquisition but enhance learning and better retention or transfer performance. Another research (Wright et al., 2016) has shown that in high CI, brain areas that are functionally significant for motor learning are recruited earlier. Lage et al. (2015) studied the correlation between different practice schedules and engagement of cortical brain areas. In their review that included 10 studies of different motor skill acquisitions, they found that there is greater activation of neural structures during random practice than during block practice. Additionally, random practice had a greater involvement of cognitive processes. On the other hand, de Xivry and Lefèvre (2015) found that different perturbation schedules did not lead to a more or less stabilized motor memory. A recent systematic review (Graser et al., 2019) of 25 studies examining the role of the practice order in children showed limited evidence for the benefit of blocked practice over random practice in regard to acquisition and retention; only for transfer there is moderate consistent evidence for the benefit of random practice over blocked practice. An additional approach of perturbation training is utilizing a split-belt training paradigm in which a person could walk on a treadmill with two belts moving at different speeds. Shimada et al. (2004) showed a significant improvement in balance function and a reduction in the number of falls (21% lower) in the split treadmill exercise. However, most falls are the result of unexpected perturbation, such as stumbling or slipping while walking, and not the result of walking on a different walking speed (Gabell et al., 1985).

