**Random, perturbation direction forward/backward/left/right; Block, perturbation direction only forward or backward or left or right. The 16 training programs. Each session lasted 20–30 min and will include 2 min of warm-up walking in participants’ own preferred walking speed without any perturbations, 14–20 min of 36 unannounced perturbations while walking, given in random direction (right, left, forward and backwards) or block direction (one direction only per training session), and 3 min of cool down walking. The perturbation training program has 18 levels of difficulty with increasing levels of perturbations (i.e., increased displacement, velocity, and accelerations of the horizontal surface translations). During each session. Note: the listed platform translation unannounced perturbations were delivered in an unpredictable randomized sequence in the directions indicated forward, backward, left, and right for random PBBT group and for the block PBBT participants to one direction only in each training session*.

We will use a perturbation treadmill (BaMPer system, see Figure 3) for providing controlled anterior–posterior (AP) and medial–lateral (ML) unannounced platform translations during treadmill walking. Both training protocols will be based on the principles of physical training and exercise prescription that include, e.g., awareness, continuity, motivation, overload, periodicity, progression, and especially the specificity principle. These important concepts are well established and accepted in the exercise physiology literature (Bhatt et al., 2012; Okubo et al., 2017; Gerards et al., 2017; Mansfield et al., 2017b; Sherrington et al., 2019). An exercise intervention targeting a certain function *must* provide a challenge/overload to the system and be progressive as well as specific to this function (Drowatzky and Drowatzky, 1999). The perturbation-based programs specifically target balance recovery reactions as follows:

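### Advance information is stated for the block arm only, so the trial can compare two programmes as delivered but cannot attribute the result to practice schedule

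*Protocol article*

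**What the plan says.** **Aim and definition.** The Abstract gives the aim: "This study aims to investigate the effect of the practice schedule (i.e., contextual interference) on reactive balance function". The Background defines blocked practice by task order alone. Its example is to "train only unexpected loss of balance to the right direction", with no announcement or cue. The primary hypothesis (Abstract, Background, Power and Sample Size Calculation) is that improvement after the block programme is not inferior to improvement after the random programme.

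**What the block arm is told.** Interventions: "Block PBBT will be trained using a foretold magnitude and unidirectional perturbations during treadmill walking", and "The participants in the block PBBT group will be aware of the direction of the perturbation, given visual cues". The Abstract agrees on direction: "the direction of the external perturbations will be announced". It does not mention magnitude.

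**What the random arm is told.** Interventions: "The random PBBT will be trained using a computer-generated random multidirectional unexpected perturbation during treadmill walking". No cue or advance notice is mentioned.

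**The contrary label.** Table 3 has a column for unannounced block perturbations. Its footnote, the Specificity section and the Overload and Progression section also use *unannounced* for both arms. Overload and Progression adds that the perturbations are unexpected in their timing under both methods.

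**The concern.** The Abstract lists what is matched between the arms: intensity, training period and concurrent cognitive tasks. Advance information is not on that list, and the text states it for one arm only. The Background argues that balance reactions evoked unexpectedly differ from other balance control and should be trained with unexpected perturbations. By that reasoning, foreknowledge could change what is being trained.

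Two things are at stake. First, a finding of non-inferiority, or a failure to find it, might be reported as an effect of contextual interference when advance information contributed to it. Secondly, the experimental treatment is described in ways that do not fully agree, so a reader cannot tell exactly what was tested.

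**Working it through.** **1. The passages side by side**

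| Item | Block arm | Random arm |
|---|---|---|
| Timing | Unexpected (Overload and Progression) | Unexpected (same) |
| Direction | Announced (Abstract); visual cues (Interventions); one per session | Four directions mixed, unexpected |
| Magnitude | Foretold (Interventions, one sentence) | Nothing stated; *unexpected* |
| General label | *Unannounced* (Table 3, footnote, Specificity, Overload and Progression) | *Unannounced* (same) |

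**2. What can be reconciled.** If *unannounced* means onset time, the label agrees with a known direction. It does not settle magnitude, which is called foretold in one place only. That the random arm is not told the magnitude is an inference from *unexpected*; no sentence says so.

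**3. Which part is separable from schedule.** All 35 perturbations of a block session share one direction, so participants would soon know it without a cue. Foretold magnitude is different: Table 3 gives each level a 2 cm range of displacement (1–3 cm at the first, 8–10 cm at the eighth) with one listed velocity and acceleration. Foretelling the level conveys little within a session. Foretelling each perturbation would convey more. The text does not say which is meant.

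**4. Why analysis cannot separate the two.** Write the block-minus-random difference as D = S + I, where S is due to schedule and I to non-schedule information. Every block participant has both and no random participant has either, so the data estimate D only.

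**5. Illustration with assumed values of I.** The documents give no value for I, so ±0.5 and ±1.0 threshold units are assumptions, as is additivity. Inputs from Table 4, fall threshold: margin 2.00, SD 2.40, n = 19 per group. Non-centrality = (2.00 + D) / (2.40 × √(2/19)), with 36 degrees of freedom. At D = 0 and one-sided 0.05 this gives power 0.809, which agrees with the 80% stated. The 0.025 column corresponds to the lower limit of the 95% CI in Statistical Analysis, read as two-sided.

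| S | I | D | P(non-inferior), 0.05 | P(non-inferior), 0.025 |
|---|---|---|---|---|
| 0 | 0 | 0 | 0.809 | 0.705 |
| 0 | −0.5 | −0.5 | 0.597 | 0.466 |
| 0 | −1.0 | −1.0 | 0.350 | 0.239 |
| −2.0 | 0 | −2.0 | 0.050 | 0.025 |
| −2.0 | +0.5 | −1.5 | 0.155 | 0.091 |
| −2.0 | +1.0 | −1.0 | 0.350 | 0.239 |

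The third and last rows are identical: no schedule effect with harmful foreknowledge looks the same as a schedule effect at the margin with helpful foreknowledge. Each row is a correct statement about the programmes (D). Only a reading as S goes wrong.

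**The case against.** The strongest reply is that the trial tests programmes. The hypothesis is worded as block training against random training, the Background asks which programme is more effective or noninferior, and randomisation supports that comparison whatever the programmes contain. This stands. A reader might infer that the trial cannot answer its question at all. The documents do not support that: only attribution to schedule is lost.

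Other stronger readings also fail:

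- **Unpredictable block sequence.** The Table 3 footnote says that "the listed platform translation unannounced perturbations were delivered in an unpredictable randomized sequence in the directions indicated", but the sentence goes on to confine block participants to one direction in each session. It does not call block direction unpredictable.
- **280 cued perturbations against none.** Eight sessions of 35 make 8 × 35 = 280 perturbations per participant. That counts exposures. The Table 3 label does not establish that no cue is given.
- **Visual cues as a second treatment.** The cue conveys direction, which one direction per session already makes largely known.
- **Trainers delivering different versions.** Nothing shows this. Perturbations are programmed in the machine, and Figure 2 and the full protocol, which may hold the instructions, are not shown.

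It is also fair to say that the 2 cm ranges limit what foretelling the level can convey, that trainees in both arms have a say in progression, and that assessment uses unannounced perturbations for both arms. These points bear on how large I might be. They do not make it zero, and equal assessment does not make the training equal. A fuller document might settle what is told, but it would not remove the disagreement in this text.

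**Conclusion.** The concern holds in a limited form. As the text stands, the arms differ in advance information as well as in schedule. The open element is chiefly magnitude: whether it is told, to which arm, and in what detail. This affects the whole block arm (25 of 50 planned participants). Its effect on the outcome cannot be sized from the documents; the figures in the illustration rest on assumed values.

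The primary non-inferiority comparison of the block programme as delivered with the random programme remains valid on this point. Attribution to practice schedule or contextual interference does not follow from it. The verdict assumes that *unexpected* means the random arm is not told the magnitude. If both arms receive the same information on magnitude, little remains beyond what the schedule itself implies.

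**What to change.** 1. Reconcile the Abstract and Interventions with Table 3, its footnote, Specificity, and Overload and Progression. Write one statement of what each arm is told about timing, direction and magnitude, and whether magnitude is told per session or per perturbation. Which version is right is for the investigators to say.
2. Record what was delivered. Trial Status puts the end of training and of baseline and post-intervention data collection at 1 March 2021, so much of this record may have to be retrospective.
3. Unless that statement shows the non-schedule information to be the same in both arms, reword the aim and primary conclusion as a comparison of an announced block programme with an unannounced random programme, without attribution to contextual interference alone.

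No change to the cueing is proposed; that would redesign the intervention during recruitment. The cost is wording and a record of delivery, with no added visits or participants. The downside is a narrower claim.

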**Figure 2 F2:**
[figure not shown]
Details of the intervention training programs.

**Table 2 T2:** Details of the perturbation parameters that were used in the pre-testing and post-testing procedures.

Perturbation size	Displacement (cm)	Velocity (cm/s)	Acceleration (cm/s^2^)
Extra small	3	0.11	0.35
Small	6	0.22	0.7
Medium	9	0.44	1.5
Medium–large	12	0.66	2
Large	15	0.88	2.5
Extra-large	18	1.20	3

*Perturbations during the pre-testing and post-testing procedures will be induced through a mechatronic device that provides controlled and unexpected AP and ML platform translations during standing and walking. Four directional perturbations (right = R/left = L/forward = F/backward = B) in a random order of each of the six magnitudes, for a total of 24 perturbations*.

**Table 3 T3:** Details of the perturbation protocols used in intervention training programs.

Training session	Platform displacement (cm)	Platform peak velocity (cm/s)	Platform peak acceleration (cm/s^2^)	Number of unannounced random* perturbations (per session)	Number of unannounced block* perturbations (per session)
1	1–3 cm	0.11 cm/s	0.35 cm/s^2^	35	35
2	2–4 cm	0.11 cm/s	0.35 cm/s^2^	35	35
3	3–5 cm	0.11 cm/s	0.35 cm/s^2^	35	35
4	4–6 cm	0.22 cm/s	0.7 cm/s^2^	35	35
5	5–7 cm	0.22 cm/s	0.7 cm/s^2^	35	35
6	6–8 cm	0.22 cm/s	0.7 cm/s^2^	35	35
7	7–9 cm	0.44 cm/s	1.5 cm/s^2^	35	35
8	8–10 cm	0.44 cm/s	1.5 cm/s^2^	35	35
9	9–11 cm	0.66 cm/s	2 cm/s^2^	35	35
10	10–12 cm	0.66 cm/s	2 cm/s^2^	35	35
11	11–13 cm	0.66 cm/s	2 cm/s^2^	35	35
12	12–14 cm	0.88 cm/s	2.5 cm/s^2^	35	35
13	13–15 cm	0.88 cm/s	2.5 cm/s^2^	35	35
14	14–16 cm	0.88 cm/s	2.5 cm/s^2^	35	35
15	15–17 cm	1.2 cm/s	3 cm/s^2^	35	35
16	16–18 cm	1.2 cm/s	3 cm/s^2^	35	35

**Random, perturbation direction forward/backward/left/right; Block, perturbation direction only forward or backward or left or right. The 16 training programs. Each session lasted 20–30 min and will include 2 min of warm-up walking in participants’ own preferred walking speed without any perturbations, 14–20 min of 36 unannounced perturbations while walking, given in random direction (right, left, forward and backwards) or block direction (one direction only per training session), and 3 min of cool down walking. The perturbation training program has 18 levels of difficulty with increasing levels of perturbations (i.e., increased displacement, velocity, and accelerations of the horizontal surface translations). During each session. Note: the listed platform translation unannounced perturbations were delivered in an unpredictable randomized sequence in the directions indicated forward, backward, left, and right for random PBBT group and for the block PBBT participants to one direction only in each training session*.

We will use a perturbation treadmill (BaMPer system, see Figure 3) for providing controlled anterior–posterior (AP) and medial–lateral (ML) unannounced platform translations during treadmill walking. Both training protocols will be based on the principles of physical training and exercise prescription that include, e.g., awareness, continuity, motivation, overload, periodicity, progression, and especially the specificity principle. These important concepts are well established and accepted in the exercise physiology literature (Bhatt et al., 2012; Okubo et al., 2017; Gerards et al., 2017; Mansfield et al., 2017b; Sherrington et al., 2019). An exercise intervention targeting a certain function *must* provide a challenge/overload to the system and be progressive as well as specific to this function (Drowatzky and Drowatzky, 1999). The perturbation-based programs specifically target balance recovery reactions as follows:

**Figure 3 F3:**
[figure not shown]
Photo of the BaMPer system. The system is composed of a motor-driven treadmill, mounted on a moving platform, with a motion controller, a safety harness, and an operator station (see text for more details).

#### Specificity

AP and ML unannounced balance loss, i.e., platform translations during treadmill walking in random order (random PBBT) or blocks (block PBBT), will be provided (Figure 2). In the random PBBT group, a software program was developed to provide random practice right/left/anterior/posterior surface translations, which was previously reported to ensure that the learned motor skill will generalize to a wide variety of situations and will optimize motor learning conditions (Drowatzky and Drowatzky, 1999; Dick et al., 2000). In the block PBBT group, anterior perturbations or posterior perturbations or right perturbations or left perturbations will be presented in separate blocks during the training session; in each session, the direction of perturbation will not be varied.

